#### Missing Data

We pursue a variety of methods to minimize biases that can occur when participants are dropped from analyses because of discontinued participation or missing data. First, we follow guidelines and procedures that have been recommended for clinical trials [139,140].

Second, our primary optimization outcome (support message engagement) will use all participants who were randomized to the study because days of support message engagement can be measured for all participants who were randomized, even if they do not complete the full 16 weeks of data collection.

Third, our Food and Drug Administration–recommended clinical outcomes (days of drinking and heavy drinking) are somewhat robust to missing data because they can be scored independently from 2 separate methods (daily EMA and TLFB at 8- and 16-week visits). Ideally, both measurement methods will contribute to the most reliable measurement of these outcomes. However, either is sufficient to score these clinical outcomes and can be used in isolation if the other method is missing (due to missing periods for daily EMA or missing study visits).

Finally, our secondary analyses use outcomes that are averaged across 2 measurement periods. This will provide a more reliable measurement for the outcomes. In instances where participants are missing a measurement, we will use multiple imputation to estimate the missing score. Multiple imputation does not attempt to estimate each missing value with a single imputed value but instead uses a random sample of imputed values. This allows for valid statistical inferences that properly reflect the uncertainty that results from missing values, such as valid SEs and CIs for parameters [141]. In brief, we will use *mice* to impute missing values in the dataset using predictive mean matching. Five distinct imputed datasets will be generated. Relevant statistical models for each secondary analysis will be fit to these imputed datasets, and parameter estimates will be averaged.

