#### Lapse Prediction Model Inputs

Input features for the lapse risk prediction model are engineered from two sources: (1) 1 time daily EMA and (2) passively sensed geolocation. Participants will complete 1 brief (less than 1 minute to complete) EMA each day. EMAs will be sent to the participant by SMS text message at 5 PM each night in the participant’s own time zone. These SMS text messages will include a link to a Qualtrics survey optimized for completion on their smartphone. A reminder to complete the survey is sent by text message at 7 PM if a participant has not yet completed it.

On each EMA, participants will report their current mood (ie, affective valence and arousal), their peak alcohol craving since their last EMA, and the occurrence and intensity of any positive events and any stressors or hassles since their last EMA. They also report how likely they are to encounter risky situations (people, places, or things) and pleasant and stressful events in the next week and how confident they are about abstaining from alcohol use in the next week. They conclude each EMA by reporting any alcohol use that they have not yet reported, the time of the start of that use, the duration of the drinking episode, and the number of drinks consumed.

Participants’ location will be continuously sensed passively using the FollowMee (FollowMee LLC) geolocation tracking app. We will increase the predictive signal from geolocation by gathering contextual information about the locations that participants visit frequently (≥2 times per month). For frequent locations, participants will report the location type (eg, home of friend, bar, restaurant, workplace, and Alcoholics Anonymous meeting location), if alcohol is typically present at that location, if they drank there previously, their typical emotional experience at that location (pleasant, unpleasant, mixed, or neutral), and the perceived risk to their recovery associated with that location. This contextual information can be gathered quickly by appending these additional questions about a newly detected frequent location to their next daily EMA.

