#### Secondary Clinical Outcomes

We will measure 2 primary clinical outcomes recommended by the Food and Drug Administration [121] for the evaluation of interventions for alcohol use disorder: number of drinking days and number of heavy drinking days in the past 30 days. These 2 outcomes are quantified at 8 and 16 weeks into the data collection period. Information about participant alcohol use is obtained from 2 sources. First, participants report episodes of alcohol use in the daily EMAs as described earlier. Second, study staff conduct a 30-day alcohol Timeline Follow-Back (TLFB) procedure [122] at the study phone visits at 8 and 16 weeks in the data collection period. The TLFB procedure is a calendar-assisted retrospective reconstruction of how many standard alcoholic drinks were consumed by the participant each day in the assessment period. This procedure is further enhanced by adding previously reported drinking episodes (dates, times, and number of drinks) from the daily EMAs to the calendar used with the participant. This provides an opportunity to validate those previous reports and collect any additional drinking episodes that may have been missed by the EMAs. The number of drinking days is defined as the number of days that any alcohol is consumed during the relevant 30-day period. The number of heavy drinking days is defined as the number of days that more than 3 or 4 standard drinks are consumed for women and men, respectively, during the relevant 30-day period. The TLFB will also be administered by study staff during the intake visit to determine inclusion or exclusion criteria (ie, time since last drink).

We will also collect secondary measures of anxiety (General Anxiety Disorder-7 [123]), depression (Patient Health Questionnaire-9 [124]), human flourishing (total score and subscales from the Flourish Measure [125]), and recovery capital (Multidimensional Inventory of Recovery Capital [126]). Each of these measures will be collected at intake and at 8 and 16 weeks into the data collection period.

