#### Secondary Analyses

Analyses for secondary outcomes will follow the same analytic plan as for the primary analyses but will use the secondary outcomes (eg, daily support message usefulness, system trust, system digital working alliance, and clinical outcomes) as the outcome variable. These analyses will allow us to determine whether the effects of message components on engagement also extend to other perceptions of the STAR system and clinical outcomes. The error distribution (Gaussian, Poisson, and negative binomial) for these generalized linear models will be selected based on the distribution of the outcome variable. These secondary analyses will use mean scores for each outcome across the 16 weeks (ie, average of scores at 8 and 16 weeks) as the dependent measure because the effects of time are not a primary focus, given the relatively short duration of the study. These analyses will only include participants who provided at least 1 measurement for the secondary outcomes during the data collection period (ie, at 8 or 16 weeks). For participants missing 1 measurement, scores will be imputed using multiple imputation (see Missing Data section).

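### Scoring 30-day drinking counts from EMA alone ignores days nobody observed and conflicts with the imputation rule; a count model for the two-visit average is also mis-scaled if plain Poisson is chosen

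*Protocol article*

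**What the plan says.** - **Outcome (Secondary Clinical Outcomes).** "The number of drinking days is defined as the number of days that any alcohol is consumed during the relevant 30-day period". Heavy drinking days are defined in the same way. Both are raw counts, taken at weeks 8 and 16.
- **Sources.** Each daily EMA has a catch-up item: "They conclude each EMA by reporting any alcohol use that they have not yet reported" (Lapse Prediction Model Inputs). At a completed visit, TLFB reconstructs every day of the window and can "collect any additional drinking episodes that may have been missed by the EMAs" (Secondary Clinical Outcomes).
- **One source missing (Missing Data).** "either is sufficient to score these clinical outcomes and can be used in isolation if the other method is missing", the stated reasons being "due to missing periods for daily EMA or missing study visits". No coverage minimum, divisor or offset goes with this rule.
- **A measurement missing (Secondary Analyses and Missing Data).** The missing week 8 or week 16 score is multiply imputed. The text does not say whether a missed visit with some EMA data counts as missing.
- **Model (Secondary Analyses).** The analyses "use mean scores for each outcome across the 16 weeks (ie, average of scores at 8 and 16 weeks"). "The error distribution (Gaussian, Poisson, and negative binomial) for these generalized linear models" is to be chosen from the distribution of the outcome.

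**The concern.** There are two separate problems.

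**Days nobody observed.** The catch-up item recovers a skipped day only if a later EMA is completed. Once a participant stops EMAs and misses the visit, neither source covers the remaining days, and a raw count adds zero for each. People who miss visits may well be the ones who stop EMAs. The components are intended to change engagement, so coverage could differ between component levels. A component that keeps people reporting would then appear to raise drinking, and one that discourages reporting would appear to lower it. The second error matters because the article would recommend a component that improves clinical outcomes even if engagement does not rise. The imputation rule would treat the same window differently, so two analysts could follow the article and obtain different data sets.

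**The average of two counts.** An average of two integers can be a half-integer, and its variance is not that of a Poisson count. The two drinking outcomes are the only day counts among the secondary outcomes, so they are the likely reason that count families are listed.

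**Working it through.** The article gives no power or precision figure for drinking days. Its only such figure, 85% power with 304 participants, concerns message engagement. It reproduces at 84.5% (152 per level, 95.2 v 98.56 days, Poisson variance, two-sided 5% assumed) and does not bear on this point.

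**A. Under-count in EMA-only windows**

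The article gives no coverage, drinking level or share of EMA-only windows, so all three are assumed. Coverage *c* is the share of the 30 days that a completed EMA look-back covers, after crediting catch-up. Drinking is taken as equally likely on covered and uncovered days.

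1. Expected score = true days × *c*. With 6 true days:

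| *c* | 100% | 90% | 80% | 60% | 50% |
|---|---|---|---|---|---|
| Score | 6.0 | 5.4 | 4.8 | 3.6 | 3.0 |

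2. Spurious contrast for a component with no true effect = (share EMA-only) × (true days) × (coverage gap between levels). With a 20% share and 6 days:
   - gap of 3 points: 0.20 × 6 × 0.03 = 0.036 days
   - gap of 5 points: 0.20 × 6 × 0.05 = 0.06 days
   - gap of 20 points: 0.20 × 6 × 0.20 = 0.24 days

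3. Within EMA-only windows, coverage of 85% v 80% gives a rate ratio of 0.85/0.80 = 1.06. Over all windows, with 20% EMA-only, it is (0.80 + 0.20 × 0.85)/(0.80 + 0.20 × 0.80) = 0.97/0.96 = 1.01.

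**B. A Poisson model on the average**

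1. Take two Poisson counts with mean μ and correlation *r*. The variance of their average is μ(1 + *r*)/2, while plain Poisson assumes μ. The ratio of model SE to true SE is √(2/(1 + *r*)): 1.41 at *r* = 0, 1.15 at *r* = 0.5, and 1 at *r* = 1.
2. The mean is modelled correctly, so the rate ratio is not biased.
3. Null simulations used 304 participants, 16 equal cells, main effects and two-way interactions, a mean of 4 days per visit and 1,000 runs. Type I error at nominal 5%:

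| Counts | Poisson, average | Poisson, sum | Average, dispersion estimated |
|---|---|---|---|
| Pure Poisson, visits independent | 0.5% | 4.7% | 5.1% |
| Strongly overdispersed (gamma shape 0.5, capped at 30) | 48% | 61% | 6.4% |

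4. Further null simulations on averages used two equal groups, gamma-Poisson participants of shape 2 or 0.7, a mean of 2 to 6 days and 400 runs per setting. Type I error was 4.8–6.5% for negative binomial and 4.0–6.0% for Gaussian. Half-integers made up 41–50% of scores.

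The first row is the scale error from averaging, and summing removes it. The second row is overdispersion: plain Poisson does worse on the sum, so summing alone is not a cure.

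**The case against.** The strongest reply is that most of this is already handled. Catch-up recovers skipped days at the next EMA, a completed TLFB covers its whole window, missing measurements go to imputation, and a coverage threshold is a detail that an article may leave to the full plan or its online repository. This stands in part: windows scored with TLFB are unaffected. However, the article does not merely leave the matter open. It declares EMA sufficient by itself, and it sets that beside an imputation rule for the same missed visit.

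Differential coverage is also unproven. EMA is a separate evening survey with adherence-based pay, not the morning message that the components alter. A 20-point gap is nearly seven times the 3% of days that the article treats as the smallest worthwhile engagement effect. This stands, and the low end of the range may be the more realistic one.

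Four stronger readings are tempting, and the article does not support them:

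- **That unreported days are scored as dry by rule.** No such rule is stated. It is what a raw count does to days that are never recovered.
- **That a count model is planned.** Gaussian is also listed and the choice is left to the data, so the fault depends on which family is chosen.
- **That averaging inflates type I error to about 50%.** That is overdispersion under plain Poisson. Averaging by itself makes the test conservative.
- **That an engaging component would be rejected.** The article recommends components that raise engagement or improve clinical outcomes, so a gain in engagement is enough.

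**Conclusion.** The point holds in limited form, and both parts deserve correction. The primary outcome and its power are untouched.

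The EMA-only rule makes no allowance for uncovered days and conflicts with the imputation rule. The resulting under-count is confined to EMA-only windows with unrecovered gaps. On the assumptions shown (6 true days, 20% EMA-only windows, coverage gaps of 3 to 20 points) the spurious contrast is about 0.04 to 0.24 days. None of these inputs comes from the article. If people drink more after they stop reporting, the under-count is larger.

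A count family for the average is a poor match. The consequence is a mis-scaled standard error under plain Poisson, at most √2 too wide for Poisson counts when visits are uncorrelated, with no bias in the rate ratio. Negative binomial and Gaussian models are little affected when counts are overdispersed.

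**What to change.** For drinking days and heavy drinking days only:

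1. Replace the two-visit average with the summed count over both windows and an offset of log(observed days). A day is observed if TLFB or a completed EMA look-back covers it.
2. Fit a negative binomial model, or use robust or estimated-dispersion standard errors. Do not use plain Poisson.
3. State the precedence. EMA-only scoring applies to windows that meet a prespecified coverage minimum, with the value set by the sponsor. Any other window without TLFB is treated as missing and multiply imputed. Say also whether an EMA-only window counts as a measurement for inclusion in the analysis.

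The cost is a small derivation from data already collected, some plan wording, and somewhat more imputed windows. The offset assumes the same drinking rate on unobserved as on observed days. The coverage minimum limits reliance on that assumption but does not remove it.

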### Ethical Considerations

The institutional research board of the University of Wisconsin-Madison Health Sciences approved this project (IRB #2024-0869). All participants will provide written informed consent and will be told they can discontinue at any time without penalty. Participants will share location data through the use of a third-party app (FollowMee). Their location data will only be identified by a randomly generated Device ID created when the app is installed. Location data are encrypted and sent to the FollowMee servers, where it will be automatically deleted after 14 days. The University of Wisconsin Cybersecurity Office has reviewed the FollowMee software, its security practices, data loss history, and encryption system for transmitting data and judged the risk of a data breach to be low. All raw data (including geolocation) will be stored on Health Insurance Portability and Accountability Act (HIPAA)–compliant servers protected behind a firewall. Raw data will be labeled with an anonymous study identification number. We also have obtained a certificate of confidentiality, which prevents the disclosure of identifiable, sensitive research information to anyone not connected to the study except with explicit consent by the participant. While we use an LLM to generate personalized support messages, no identifiable participant data will be passed into the LLM. It will only be given up to 4 pieces of information about the participant: lapse probability (high, moderate, or low), trend in lapse probability (increasing, decreasing, or stable), one important lapse feature category selected from several categories, and preferences for style and tone.

## Results

The National Institute on Alcohol Abuse and Alcoholism funded this project (R01AA031762) on August 9, 2024, with a funding period from August 20, 2024, to July 31, 2029. Enrollment will begin in December 2025. We plan to recruit participants for approximately 3 years.

## Discussion

Clinical observation and research suggest that successful recovery from alcohol use disorder requires long-term and perhaps lifelong self-monitoring of lapse risk. Self-monitoring, however, is difficult given the dynamic and complex interplay of numerous risk factors over time.

Machine learning lapse prediction models are now emerging. Recovery monitoring support systems that synthesize these developments can potentially guide patients toward personally risk-relevant engagement that is adaptive, efficient, and more effective. Research is needed to determine the optimal feedback from embedded machine learning prediction models such that patients make the best use of these automated capabilities.

The optimization study in this project is guided by the MOST framework. The research in this project focuses on the MOST optimization phase. We propose to optimize feedback from a lapse prediction model (via daily engagement messages) both to increase engagement with a recovery monitoring support system and to improve clinical outcomes. We will evaluate the effects of 4 message components (lapse probability or lapse probability change, an important feature, a risk-relevant module recommendation, and tone personalization) that comprise the daily engagement messages and can make the output from our machine learning model more transparent to participants. Completion of our specific aims sets the stage for future, programmatic MOST research to evaluate optimized recovery monitoring support systems using appropriate designs (eg, randomized controlled trial) for that subsequent phase of development.

Additionally, the optimization components use output that would be available from any machine learning lapse prediction model such that conclusions about the impact of these components on engagement can generalize beyond our specific machine learning model. Similarly, engagement messages including these message components could be used in any recovery monitoring system or digital therapeutic for alcohol use disorder, allowing conclusions to generalize to current and future system variants. At the conclusion of the grant period, we will also deliver this optimized recovery monitoring support system as a tangible product and model for how to embed sensing and machine learning into other existing systems.

## Appendix

Multimedia Appendix 1 Peer review report by the National Institute on Alcohol Abuse and Alcoholism (R01AA031762).

## Abbreviations

DSM-5: Diagnostic and Statistical Manual of Mental Disorders (Fifth Edition)
EMA: ecological momentary assessment
HIPAA: Health Insurance Portability and Accountability Act
LLM: large language model
MOST: Multiphase Optimization Strategy
OSF: Open Science Framework
STAR: Smart Technology for Addiction Recovery
TLFB: Timeline Follow-Back
